## Abstract

**Introduction:**

As COVID-19 is spreading, new psychological health problems are suspected to be emerging among pregnant women. Higher maternal mental health distress, including perinatal anxiety, depression, and COVID-19-specific phobia, is supposed to be increasing during the pandemic, which impacts pregnant women’s health and their infants and calls for intervention. Due to the social distancing protocols posed by the pandemic, telemental health interventions have fast become the most common form of psychosocial support for maternal mental health. However, there is no evidence of the effectiveness of maternal low-intensity psychosocial telemental interventions in improving mental health outcomes. The trial’s objective is to evaluate the clinical efficacy of telemental low-intensity psychosocial interventions in pregnant and postpartum women attending the Women Wellness and Research Centre in Qatar in the era of the COVID-19 pandemic.

**Methods and analysis:**

The clinical trial is randomized in which pregnant women will be assigned equally through block randomization between two arms: (1) a control group and (2) an intervention group. The primary endpoint is the perinatal psychological distress, including perinatal depression, anxiety, and COVID-19 phobia in their third trimester; the secondary, tertiary, fourth, and fifth endpoints will be in the postnatal period (3–5 weeks, 2–4 months, 5–7 months, and 8–10 months). This trial involves pregnant women in their second trimester with no mental health illness history who communicate in English and Arabic and consent to participate. A sample size of 58 (29 participants per arm) is targeted.

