#### Phase two: screening and enrolling participants

The investigators will follow the Consolidated Standards of Reporting Trials (CONSORT) in displaying steps of recruitments and randomization. The eligible participants will be selected randomly from the registered pregnant women at Women Wellness and Research Centre (WWRC) and will be contacted by phone to inform the study through verbal informed consent.

Randomization (1:1) with an automated online system ensuring that the research team will not affect randomization. Participants will complete all the assessments via telephone interviewing but following a prewet transcript, and therefore, their responses could be affected by the trial team. A cohort of participants will be followed from the time of approval of the study until the end of interventional sessions (T5-session 6), approximately 1 year after the baby is born. Figure 1 summarizes the study flow.

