#### Intervention description {11a}

##### Intervention group (IG)

This a series of Low-Intensity Psychological Interventions based on the healthy thinking manual. The Thinking Healthy approach attends to giving attention to overall maternal mental well-being by delivering a simplified form of cognitive behavior therapy (CBT) recommended by the Mental Health Gap Action Programme (mhGAP) [19]. It will be tailored and delivered through six video conferencing sessions, real-time interaction between patients and therapists via VSee video connection. Each session is a one-to-one session and may last up to 45 min. Adherence will be monitored and documented on logbooks and medical records. Details about the sessions are available in the WHO manual.

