### Participant timeline {13}

Prospectively, the participants will be followed for approximately 1 year (from their second trimester to around 8 to 10 months postnatal). Participants will be enrolled and assessed following the Standard Protocol Items: Recommendations for Intervention Trials (SPIRIT) schedule as shown in Table 1.

**Table 1 Tab1:** SPIRIT schedule

	Study period						
	Screening	Allocation	Post-allocation				
	Pregnancy		Pregnancy		Postpartum		
Timepoint**	***T-***_***1***_	**0**	***T***_***0***_	***T***_***1***_	***T2***	***T3***	***T5***
Eligibility screen	X						
Informed consent	X		X	X	X	X	X
Randomization		X					
Interventions:							
				X	X	X	X
Telemental low-intensity psychosocial interventions A							
Control Group B				X	X	X	X
Assessments:							
1. Mental health history	X						
2. Medication use	X						
3. COVID-19 status			X	X	X	X	X
4. Perinatal depression			X	X	X	X	X
5. COVID-19-specific phobia			X	X	X	X	X
6. Perinatal anxiety			X	X	X	X	X
7. Sociodemographic characteristics			X	X	X	X	X
8. Pregnancy-related factors			X	X			
9. Acute medical problem			X	X	X	X	X
10. Previous maternal and neonatal complication			X	X			
11. Chronic illnesses			X	X			
12. Behavioral factors			X	X	X	X	X
13. Stressful life events			X	X	X	X	X
14. Newborn health					X	X	X

*T*_*−1*_ before enrolment it is the screening phase in the 2nd trimester [14th week until the end of 27th], *T*_*0*_ after randomization and allocation it is baseline assessment [14th week until the end of 27th], *T*_*1*_ is during the 3rd trimester [28th week until the end of 42nd week] the first intervention session, *T*_*2*_ during early postpartum 3–5 weeks, *T*_*3*_ in 2–4 months postpartum, *T*_*4*_ in 5 to 7 months postnatal, *T*_*5*_ in 8 to 10 months postnatal

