### Outcomes {12}

#### Primary outcomes

The primary outcomes are baseline (T0) scores of perinatal depression, perinatal anxiety, and COVID-19-specific phobia during late pregnancy and during the follow-up up to 10 months postpartum, additionally computing the changes in the scores from the baseline [(T1–T0), (T2–T1), (T3–T2), (T4–T3), and (T5–T4)].

We will evaluate the primary outcomes through video conferencing sessions via VSee video connection based on standard tools.

Edinburgh Postnatal Depression (EPDS-10) will be used to assess perinatal depression. The scale showed to be a reliable screening tool in Qatar [9]. Cumulative evidence demonstrated a pooled sensitivity of 0.80 and a pooled specificity of 0.81 [21].

The anxiety subscale of EPDS-3A will be used to assess perinatal anxiety. It is identified to have acceptable sensitivity and specificity based on a systematic review of perinatal anxiety tools [22].

Corona-specific phobia, a severe fear specific to the emerging virus, will be assessed through the Corona-Specific Phobia questionnaire that consists of a seven-item scale. Answers are based on the five-item Likert-type scale, and it showed internal consistency (*α* = 0.82) with robust psychometric properties. A total score is calculated by adding up each item score (ranging from 7 to 35). The higher the score, the greater the fear of coronavirus-19 [23].

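### The primary timepoint is defined inconsistently, and the only ranking given (abstract) puts first an assessment that follows at most one of six sessions

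*Protocol article*

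**What the plan says.** Three parts of the protocol article bear on which timepoint is primary.

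- **Abstract, Methods and analysis.** "The primary endpoint is the perinatal psychological distress, including perinatal depression, anxiety, and COVID-19 phobia in their third trimester". The postnatal assessments are ranked after it: "the secondary, tertiary, fourth, and fifth endpoints will be in the postnatal period (3–5 weeks, 2–4 months, 5–7 months, and 8–10 months".
- **Outcomes {12}, Primary outcomes.** Scores on the three scales are primary at baseline, "during late pregnancy and during the follow-up up to 10 months postpartum", together with the five successive changes from T1–T0 to T5–T4.
- **Statistical methods {20a}.** A mixed model with a time-by-group interaction estimates the treatment effect at each timepoint. None is singled out as primary.

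Three parts describe when treatment is given.

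- **Participant timeline {13}, Table 1 and footnote.** T0 comes "after randomization and allocation it is baseline assessment [14th week until the end of 27th" week. T1 "is during the 3rd trimester [28th week until the end of 42nd week] the first intervention session". The intervention row has no mark before T1, and all three scales are scheduled at T1.
- **Intervention description {11a}.** The programme is "delivered through six video conferencing sessions, real-time interaction between patients and therapists via VSee video connection".
- **Phase two: screening and enrolling participants.** Follow-up runs "until the end of interventional sessions (T5-session 6), approximately 1 year after the baby is born". The Table 1 footnote places T5 at 8 to 10 months postnatal.

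**The concern.** The stated objective is superiority of the telemental programme, and the Discussion says the results will inform whether it joins the antenatal package. The primary comparison therefore has to be made where the programme has had a chance to act, and the reader has to know in advance which comparison that is.

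Neither condition is met. Two sections define the primary outcome differently and the analysis section does not settle it. Where timepoints are ranked, the one placed first coincides with the start of treatment. If the abstract's ranking governs, a null result at T1 could be reported as failure of the programme when the arms had differed by one session at most. If the Outcomes section governs, no single comparison decides the trial.

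**Working it through.** **1. Exposure at each assessment.** Assume one session per timepoint from T1 on, as the footnote and the T5 = session 6 label suggest. The documents do not say whether the scales come before or after that day's session, so each timepoint has two possible counts.

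| Timepoint | Scales before session | Scales after session |
|---|---|---|
| T1 | 0 | 1 |
| T2 | 1 | 2 |
| T3 | 2 | 3 |
| T4 | 3 | 4 |
| T5 | 4 | 5 |

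At T1 this is 0/6 to 1/6 of the course (0 to 17%). T1 to T5 gives five intervention contacts, not six. The count reaches six at T5 only if T0 is counted as a contact. In that case there are five treatment sessions and T1 exposure is at most 1/5.

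**2. The plan's sample size.** Inputs from Statistical methods {14}: p1 = 0.34, p2 = 0.70, two-sided alpha 0.05, power 80%, ratio 1. With pooled variance under the null (Fleiss, no continuity correction):

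n = [z(0.975)·√(2p̄(1−p̄)) + z(0.80)·√(p1(1−p1) + p2(1−p2))]² / (p1−p2)²

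p̄ = (0.34 + 0.70)/2 = 0.52, so n = [1.960 × 0.7065 + 0.8416 × 0.6591]² / 0.36² = 29.03. The stated 29 per arm is reproduced, with power 79.96%. The formula as printed in the article is unpooled and gives 26.3. That does not affect this point.

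The 0.34 is attributed to studies reporting improvement once the interventions had been delivered. The 36-point difference is therefore a post-treatment difference.

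**3. Power if only part of that difference is present.** This step is an assumption, because the documents give no effect for T1 or any other timepoint. Hold controls at 0.70, set p1 = 0.70 − 0.36f and n = 29 per arm:

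power = Φ{[(p2−p1)·√n − 1.960·√(2p̄(1−p̄))] / √(p1(1−p1) + p2(1−p2))}

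| Share f of full difference | p1 | Power | n per arm for 80% |
|---|---|---|---|
| 1 | 0.34 | 80% | 30 |
| 5/6 | 0.40 | 64% | 42 |
| 1/2 | 0.52 | 29% | 115 |
| 1/3 | 0.58 | 15% | 250 |
| 1/5 | 0.628 | 8% | 675 |
| 1/6 | 0.64 | 7% | 963 |

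Worked line for f = 1/2: p̄ = 0.61, (0.18 × 5.385 − 1.960 × 0.6898)/0.6779 = −0.564, and Φ(−0.564) = 0.286.

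**4. Which later timepoint.** If benefit were proportional to sessions received (again an assumption), T2 would carry 1/6 to 2/6 of the difference, with power 7 to 15%, so moving the primary from T1 to T2 gains little. T4 (3/6 to 4/6) would give 29 to 46%, and T5 (4/6 to 5/6) 46 to 64%. The 4/6 value uses p1 = 0.70 − 0.24 = 0.46: (0.24 × 5.385 − 1.960 × 0.6980)/0.6771 = −0.112, Φ = 0.46. An average over T2 to T5 would reflect (1+2+3+4)/4 = 2.5 or (2+3+4+5)/4 = 3.5 sessions, which is below T5 either way.

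**The case against.** The strongest reply is that the Outcomes section, not the abstract, is where a protocol defines its endpoints. That section already makes the postnatal scores primary, and the mixed model uses all of them. This stands in part. The third-trimester-only endpoint comes from the abstract alone, and the trial will have data from well-treated women whichever definition is used. It does not remove the problem, because the Outcomes section lists many scores and changes without choosing among them, and the abstract is the only text that does choose.

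A reader might go further and infer that the trial's primary comparison as a whole precedes treatment, so that a null result is close to certain with a 5% chance of significance. The documents do not support that, for these reasons:

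- On the wording of the Outcomes section, T2 to T5 are primary too.
- That the scales and the session share one contact at T1 is an inference. The Outcomes section refers to video sessions, but Phase two says assessments are by telephone interview. Their order is not given, and T1 spans weeks 28 to 42.
- Benefit in proportion to session count is not stated anywhere. A first session could do more or less than a sixth of the work.
- Three scales are primary and no adjustment is stated. With no effect, the chance of at least one significant result would be 1 − 0.95³ = 14% if the scales were independent, not 5%.

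The session-count mismatch may also be one of labelling, since T0 to T5 makes six contacts. The study-flow figure, which might show the mapping, is not available here. None of these readings puts more than one treatment session at or before T1.

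**Conclusion.** The point holds in this form: the primary timepoint is defined in two incompatible ways, and the only ranking in the article selects T1, where zero or one of six sessions has been delivered. That follows from the article's own definitions, given that its first-session label for T1 is taken at face value.

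The size of the consequence rests on an assumption about how much benefit exists by T1. Power at 29 per arm ranges from 80% (all of it) through 29% (half) and 15% (a third) to 7% (a sixth). Even if the first session delivered half the full benefit, a null T1 result would be more likely than not. Such a result would say little about the programme, but it is not assured.

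**What to change.** - Name one primary timepoint late in the course: the group difference at T5 (8–10 months postnatal) from the planned mixed model, or at T4 if the sponsor gives more weight to limiting dropout. Do not use T2, which follows only one or two sessions.
- Make T1 and the other earlier timepoints secondary.
- State whether the scales are completed before or after that day's session content.
- Use the same definition in the abstract, Outcomes {12}, Statistical methods {20a} and the registry.
- Reconcile the six-session course, T1 as the first session, and T5 as session 6. Which session schedule is right is for the sponsor to decide.

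The cost is a protocol amendment and a registry update. No visits are added, since scores at T4 and T5 are already among the planned outcomes, and the Trial status section says recruitment has not begun. The main downside is greater loss to follow-up at a late timepoint, which the Discussion already names as a challenge. On the proportional illustration, T5 improves power to 46–64% but does not restore 80%, so the sponsor should state what effect it expects at the chosen timepoint and check that 29 per arm still suffices.

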**Discussion:**

This study will provide recommendations about the efficacy of low-intensity psychosocial maternal telemental interventions to be implemented as a preventive service.

**Trial registration:**

2a-ClinicalTrials.gov NCT04594525. Registered on October 20, 2020.

**Supplementary Information:**

The online version contains supplementary material available at 10.1186/s13063-021-05339-w.

## Introduction

### Background and rationale{6a}

The infectious outbreak of the novel coronavirus was first identified in Wuhan City, China, and reported to the World Health Organization (WHO) on December 31, 2019. COVID-19 caused by severe acute respiratory syndrome coronavirus 2 (SARS-CoV-2) has been widely publicized as “killer pneumonia” transmitted via droplets and fomites during close unprotected contact between an infector and infected with no precise treatment [1]. The life-threatening aspect of COVID-19 was vividly described by the media, constantly alarming people of the dangers of this disease. In addition to the actual physical health danger posed by the virus, the pandemic has also impacted mental health [2].

Perinatal depression and anxiety are increasingly recognized as crucial public health issue [3]. Emerging infectious outbreak decreases social support and fuels perinatal mental health disorders. For instance, a previous infectious outbreak revealed that pregnant women tend to overestimate the risk of contracting respiratory illness and report higher anxiety levels [4]. Recent data show a higher prevalence of psychological distress (anxiety and depression) in pregnancy during the COVID-19 pandemic across several countries [5–7].

During the pandemic, the burden of perinatal health problems reported in Qatar was higher than before the pandemic; perinatal depression increased by 10% (24% vs. 34.4%), and perinatal anxiety increased by 22.8% (16.4% vs. 39.2%). These studies reported the prevalence based on screening tools and utilized similar conceptual definitions in distinguishing depressed and anxious pregnant women from those without outcome [8–10]. The alarming rise in perinatal mental health distress may negatively affect the expecting mothers and their offspring leading to an increase in the infants’ risk of pre-term delivery and neurodevelopmental disorders [11]. Crucial interventions are needed to address perinatal psychological distress among Qatar’s maternal population during the pandemic.

Most guidelines recommend psychological or behavioral treatments as first-line therapy for pregnant women with mild to moderate depression [12], considering it an essential strategy for mitigating postnatal depression and preventing behavioral and developmental problems in upcoming children [13, 14], supported by the United States Preventive Services Task Force (USPSTF) recommendation [15].

In infectious pandemics and emergencies, telemental health is a practical strategy that reaches the population [16, 17]. The outcome of systematic analysis of RCTs (randomized controlled trials) showed the effectiveness of telemental service in the general population, leading to a significant reduction in anxiety, depressive symptoms, distress, and fear [18]. However, no substantial evidence on the effectiveness of Telemental health intervention among the pregnant population.

### Objectives {7}

The objectives are as follow: to assess the impact of telemental low-intensity psychosocial interventions on perinatal mental health outcomes, through assuming the superiority of the telemental health intervention on the control arm in improving perinatal psychological distress among the perinatal population, and working on rejecting the null hypothesis stating that pregnant women receiving low-intensity psychosocial interventions have the same psychological distress (perinatal depression, perinatal anxiety, and COVID-19 phobia) compared to pregnant women not receiving the intervention during the COVID-19 pandemic.

The following research questions will be addressed:
What is the effect size of telemental health on perinatal mental health outcomes?What are the period prevalence and incidence of perinatal depression, anxiety, and COVID-19 phobia among perinatal women during the COVID-19 pandemic in Qatar?What other factors influence perinatal mental outcomes during the COVID-19 pandemic in Qatar?

### Trial design {8}

A randomized controlled, parallel trial of the effect of low-intensity psychological maternal telemental health intervention on perinatal psychological outcomes among pregnant and postpartum women.

The study will be carried in two phases.

#### Phase one: training of psychologists

The investigators will train two psychologists that are English and Arabic speakers on the WHO materials [19]. Consequently, the data collectors will be prepared to undertake the approved research, motivate interviewers, and ensure the good overall quality of data. The training includes both formal classroom training and hands-on experience with telemedicine techniques.

#### Phase two: screening and enrolling participants

The investigators will follow the Consolidated Standards of Reporting Trials (CONSORT) in displaying steps of recruitments and randomization. The eligible participants will be selected randomly from the registered pregnant women at Women Wellness and Research Centre (WWRC) and will be contacted by phone to inform the study through verbal informed consent.

Randomization (1:1) with an automated online system ensuring that the research team will not affect randomization. Participants will complete all the assessments via telephone interviewing but following a prewet transcript, and therefore, their responses could be affected by the trial team. A cohort of participants will be followed from the time of approval of the study until the end of interventional sessions (T5-session 6), approximately 1 year after the baby is born. Figure 1 summarizes the study flow.

**Fig. 1 Fig1:**
[figure not shown]
Study flow

## Methods: participants, interventions, and outcomes

The manuscript is written in accordance with the Standard Protocol Items: Recommended items to address in a clinical trial protocol and related documents (SPIRIT) guidelines.

### Study setting {9}

The WWRC is the primary setting for screening and recruiting the participants. The WWRC is a paramount governmental health facility that provides continuous health services for women during their reproductive age, following them from antenatal to postnatal. The center accommodates 17,000 births per year. The WWRC is highly accessible and affordable by the country’s population. WWRC’s patient cohort offers a good representation of the whole community. The average number of patients attending each clinic can reach 20 per shift. WWRC’s antenatal clinic participation rate was as high as 70% of the total live births during 2019 (about 12,896 pregnant women) [20].

### Patient recruitment and study procedures

#### Eligibility criteria {10}

##### Patient inclusion and exclusion criteria

The target population is perinatal women following up at the Women’s Wellness and Research Centre (WWRC). The inclusion criteria include all pregnant women aged 18 and above in their second trimester who agree and consent to receive teleconsultation. Participants need to communicate in English and Arabic. However, there is no specific nationality restriction. We will exclude pregnant women who cannot download the Virtual Single Execution Environment (VSee) application and those with psychiatric illness. Furthermore, pregnant women receiving mental health medications and following up at Sidra hospital or Hamad Medical Corporation mental health services will be excluded.

#### Who will take informed consent? {26a}

The consent will be taken by delegates’ obstetrics and gynecology physicians of the approved representatives from WWRC in the screening phase through the phone. In the data collection phase, the psychologists will take consent at the beginning of the video call prior to the interview.

#### Additional consent provisions for collection and use of participant data and biological specimens {26b}

No biological specimen is required in the study; it is a psychosocial intervention. Consents are available upon request.

#### Plans to promote participant retention and complete follow-up {18b}

For adherence to the intervention, participants in both groups will be contacted by phone every 3 weeks.

For adherence to questionnaires, psychologists will collect the data through interviews, less commonly to have missing data. In case of missing data, study participants will be contacted and reminded about the completion by a psychologist through telephone.

